### 2.4. Intervention

All interventions will consist of an 8-week individually tailored exercise program based on each participants’ physical fitness level. This duration reflects a balance between effectiveness and feasibility [81]. Detailed descriptions of the interventions are provided in the supplementary Template for Intervention Description and Replication (TIDieR) checklist (Supplementary File S1).

HIIT and CAT will be performed twice weekly for 8 weeks on a cycle ergometer under the supervision of a physiotherapist. The HIIT consists of 5–6 45 s bouts of high-intensity bursts at 85–95% of peak load reached during a CPET, alternating with low-intensity 90 s bouts at an intensity below the first ventilatory threshold. CAT consists of two 20 min bouts at intensities below the first ventilatory threshold interspersed with 2 min breaks.

The participants in the MA group will receive information on physical activity based on the Dutch physical activity guidelines, which recommend engaging in at least 150 min of continuous moderate-to-vigorous-intensity physical activity per week and performing muscle-strengthening exercises on two days per week [82]. To support self-monitoring, each participant will be provided with a Fitbit smartwatch to track daily step counts throughout this study. The average daily step count recorded during the baseline phase will serve as the individualized reference point for their movement goals. During the eight-week intervention period, participants in the MA group will be encouraged to increase their daily step count by approximately 3000 steps on at least five days each week, relative to their personal baseline [83].

### 2.5. Statistical Analysis

Statistical analyses will be conducted using R or Stata, with the significance set at *p* < 0.05 (two-tailed). The primary analysis will follow the intention-to-treat principle and per protocol analysis will be performed as a sensitivity analysis.

Continuous variables will be presented as mean (SD) or median [IQR] values based on normality. Categorical variables will be reported as frequency (%). Normality will be assessed using histograms and Q-Q plots. In case normality assumptions are violated, a log-transformation will be explored.

Baseline characteristics, including age, sex, disease severity, anxiety, depression, and medication use, will be presented for each intervention arm and for each disease type (PD, MS) using descriptive statistics.

Linear mixed models (LMMs) will be used to analyze the longitudinal changes in anxiety and depression across time points (baseline, intervention, and follow-up) and between intervention arms (HIIT, CAT, and MA). These factors will be added to the model as fixed factors. All outcomes will serve as dependent variables in separate models. Participant ID will be added to the model as a random effect to account for intra-individual correlations. Age, sex, medication, and mobility severity (i.e., TUG) will be added to the model as covariates and interaction effects for disease will be investigated. Exploratory subgroup analyses will be conducted if the interaction term is significant. The MA group will be the reference group.

The analyses of secondary outcomes will be exploratory in nature. No formal adjustment for multiple comparisons will be applied; exact *p*-values will be reported, and the results will be interpreted cautiously considering the increased risk of Type I error.

For all primary and secondary outcomes, estimated effects with 95% confidence intervals will be reported from the LMM, alongside standardized effect sizes (Hedges’ g with 95% confidence interval) to facilitate clinical interpretation.

Missing data will be expected, but LMMs are generally robust to missing data. Outliers will be identified using residual diagnostics and sensitivity analyses will be performed with and without outliers to evaluate robustness.

To examine the associations between markers of neuroplasticity and neurodegeneration, and motor and non-motor symptoms, Pearson’s or Spearman’s correlation coefficients will be used depending on normality. Associations will be assessed for changes over time, specifically for the intervention phase.

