## Abstract

**Background/Objectives:** Parkinson’s disease (PD) and multiple sclerosis (MS) are neurological conditions that result in debilitating non-motor symptoms, such as anxiety and depression, which significantly reduce quality of life and often persist despite pharmacological treatment. As a result, effective alternative treatment strategies are needed. Exercise therapy—particularly aerobic training—has shown promise in alleviating non-motor symptoms, potentially through neuroplastic adaptations. However, traditional aerobic exercise is often time-consuming and monotonous, limiting long-term adherence. High-intensity interval training (HIIT) offers a time-efficient and potentially more engaging alternative, though its effects on non-motor symptoms in PD and MS remain understudied. **Methods**: This transdiagnostic randomized controlled trial will enroll 48 participants (24 PD, 24 MS) with clinically significant affective symptoms (hospital anxiety and depression scale [HADS] ≥ 8). The participants will be randomly assigned to one of three 8-week interventions: (1) HIIT, 5–6 intervals of 45 s of high-intensity cycling; (2) continuous aerobic training (CAT), 50 min of low-intensity cycling; (3) movement advice (MA), step goals, and physical education. The primary (affective symptoms) and secondary outcomes (cognition, fatigue, sleep, motor function) will be assessed at four time points: 4 and 1 weeks pre intervention, and 1 and 4 weeks post intervention. Weekly blood samples and pre/post brain imaging will be collected to study biofluid and MRI measures for potential neuroplasticity. Linear mixed models will analyze the time and group effects. **Discussion:** This trial will assess whether HIIT can more effectively improve non-motor and motor symptoms in PD and MS than CAT or MA. A multimodal approach will explore both the clinical outcomes and underlying mechanisms, informing scalable and engaging rehabilitation strategies.

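### The primary mixed model names arm and time but no arm-by-time term or baseline-adjusted contrast, so fitted as written its arm effect averages pre- and post-intervention HADS scores

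*Protocol article*

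**What the plan says.** Section 2.5 sets out the primary analysis as linear mixed models of "changes in anxiety and depression across time points (baseline, intervention, and follow-up) and between intervention arms (HIIT, CAT, and MA"). It then says how time and arm enter: "These factors will be added to the model as fixed factors". The other stated terms are a participant random effect, four covariates (age, sex, medication, TUG) and one interaction: "interaction effects for disease will be investigated". On the contrasts it says only "The MA group will be the reference group". The Abstract gives the same picture: "Linear mixed models will analyze the time and group effects".

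The visits are described in three places:

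- **Abstract:** outcomes are assessed at "4 and 1 weeks pre intervention, and 1 and 4 weeks post intervention".
- **Section 2.3:** baseline, week 4, week 12 (post-intervention) and week 16 (follow-up).
- **Table 1:** HADS at weeks 1, 4, 13 and 16. Weeks 5 to 12 are headed Intervention, and weeks 13 and 16 both stand under Follow-Up.

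Section 2.2.2 sizes the trial on improvements in HADS total of 6 points (HIIT) and 3 points (CAT), with SD 6, alpha 0.05 and 80% power. It uses a repeated measures ANOVA and arrives at 42 participants before dropout.

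**The concern.** The trial asks whether affective symptoms improve more under HIIT than under CAT or MA. That is a difference between arms in change, or equivalently a difference after the intervention given the starting level. In a repeated-measures model that keeps the pre-intervention scores as outcomes, the arm-by-time term carries this difference. The arm main effect does not: it pools the pre-intervention visits, where randomization makes the expected difference zero, with the post-intervention visits.

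An analyst who fits exactly the terms listed would thus test a diluted quantity as the primary result. An analyst who adds the interaction would be choosing a model that the text does not name, and could make that choice after seeing the data. The loose time labels add a second choice: which HADS visits belong to which level of the time factor.

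**Working it through.** **Inputs from the documents.** HIIT improvement 6 points, CAT 3 points, SD 6, alpha 0.05, power 80%, N = 42 (section 2.2.2); two-tailed testing (section 2.5); two HADS visits before and two after the intervention (Abstract, Table 1). Then 42/3 = 14 per arm.

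**Assumed, because not given.** A common correlation rho between any two HADS visits, shown for 0.3, 0.5 and 0.7; the same SD at every visit; complete data; no expected arm difference before the intervention.

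**1. The plan's own figure.** d = (6 − 3)/6 = 0.5, so f = 0.25. For the within-between (arm-by-time) interaction with 3 groups, 2 measurements and rho 0.5 (options assumed):

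- lambda = f² × N × m/(1 − rho) = 0.0625 × 42 × 2/0.5 = 10.5, on 2 and 39 degrees of freedom
- power = 0.803

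So N = 42 is reproduced as an interaction test. The G*Power options are not stated, and another route also gives 42: a between-arm test with 4 measurements, rho 0.5 and an assumed MA improvement of 0 (f = 0.41, power 0.83). The link to the interaction is plausible but not proven.

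**2. What the additive arm coefficient estimates.** With balanced data and a participant random effect, the HIIT-minus-CAT difference in arm coefficients equals the difference in person means over the four visits. If the true difference is 0, 0, 3, 3:

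- (0 + 0 + 3 + 3)/4 = 1.5 points

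If only one pre-intervention visit entered with two later ones, it would be (0 + 3 + 3)/3 = 2.0 points.

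**3. Power under three analyses.** HIIT versus CAT, 14 per arm, SE = SD × √(2/14), two-sided noncentral t with 26 degrees of freedom:

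- A, additive arm effect: SD of the four-visit mean = 6√((1 + 3rho)/4), difference 1.5
- B, first post-intervention visit adjusted for the mean of the two pre-intervention scores: residual SD = 6√(1 − 2rho²/(1 + rho)), difference 3
- C, mean of both post visits minus mean of both pre visits: SD = 6√(1 − rho), difference 3, with the effect persisting to week 16

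| rho | A: SD, power | B: SD, power | C: SD, power |
|---|---|---|---|
| 0.3 | 4.14, 15% | 5.57, 28% | 5.02, 33% |
| 0.5 | 4.74, 13% | 4.90, 34% | 4.24, 44% |
| 0.7 | 5.28, 11% | 3.91, 50% | 3.29, 64% |

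A simulation of 300 mixed-model fits at rho 0.5 gave a mean absolute coefficient of 1.57 with 14% power for A, and 2.92 with 45% for C.

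**4. If the effect has gone by week 16.** A falls to (0 + 0 + 3 + 0)/4 = 0.75 points. C also halves, to 1.5 points, with power 12%, 15% and 21% for rho 0.3, 0.5 and 0.7. B is unchanged, because it uses only the first post-intervention visit.

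**5. Time labels against visits.** Section 2.5 has three labels and HADS has four visits. By Table 1, no HADS falls under Intervention and both later visits fall under Follow-Up. By section 2.3, the week 12 visit could carry the intervention label and week 16 the follow-up label. The two give different time factors. Under either, two of the four HADS values per participant are pre-intervention, so step 2 is unaffected.

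**The case against.** The strongest reply is that section 2.5 omits the interaction without excluding it. Its declared purpose is to study longitudinal changes between arms, which is what an interaction does. Section 2.1 cites within-subject modelling as a source of power, and N = 42 can be reproduced as an interaction test. The article is also condensed, and a SAP may exist. This stands to the extent that the interaction may well be intended, and it would be wrong to say that the plan rules it out. It does not remove the point. The article goes beyond silence: it lists the terms, says how arm and time enter, and names a different interaction, and the Abstract repeats time and group effects.

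A reader might make three stronger inferences that the documents do not support:

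- *The intervention level of time is empty.* This follows from Table 1 alone. Section 2.3 places the post-intervention visit at week 12, the last intervention week, which would fill that level. Section 2.5 also applies separate models to all outcomes, and some (VAS, PASIPD, blood) do have values during the intervention. What is established is a mismatch of labels and a week 12/13 discrepancy.
- *The random effect makes intervals for change too narrow.* The text says "Participant ID will be added to the model as a random effect to account for intra-individual correlations". It does not say that this is a random intercept alone, gives no residual structure, and gives no correlations between visits. With equal correlations there would be no such bias.
- *Correcting the model raises power from 13% to 44%.* The 44% (rho 0.5) belongs to the contrast averaging both post visits with a lasting effect. For a single first post-intervention visit the figure is about 34%.

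**Conclusion.** The point holds as a defect in the stated primary model. Fitted as written, the arm effect is half the post-intervention difference: 1.5 points for a true 3. The halving rests on both pre-intervention visits entering as outcomes with equal weight and on an effect that lasts to week 16. It does not depend on rho.

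The power loss does depend on rho, which is assumed. Over 0.3 to 0.7 the additive test has 11% to 15%, against 28% to 50% for the baseline-adjusted contrast at the first post-intervention visit. None of these reaches 80%, so restating the model corrects what is tested but does not by itself secure the planned power. The mismatch between labels and visits is a separate, smaller inconsistency that needs reconciling whichever model is used.

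Because this is the primary analysis, it should be corrected before any data are analysed.

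**What to change.** In section 2.5:

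- Define time as the four actual HADS visits.
- Add the arm-by-visit interaction, or model the post-intervention scores with the mean of the two pre-intervention HADS scores as a covariate.
- Name the arm contrast at the first post-intervention visit as the primary effect and the same contrast at the follow-up visit as durability. With MA as reference, state the HIIT-versus-CAT contrast explicitly, since the sample size is built on it.
- Bring the Abstract's description into line.

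Reconcile the week 12 visit in section 2.3 with week 13 in Table 1, and use the same labels in the model.

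An unstructured covariance and Kenward-Roger degrees of freedom are reasonable options for the SAP, but the article does not need them. The change costs wording only: no new data, visits or participants. Section 2.1 gives the status as enrollment and data collection, so it can still be made and dated before analysis.

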## 2. Materials and Methods

### 2.1. Study Design and Setting

This is a single-blind, monocenter, randomized trial, with serial baseline–intervention–follow-up periods and three parallel intervention arms (see Figure 1). The total study duration per participant is 16 weeks and it will be conducted at Amsterdam UMC. All participants will perform two baseline assessments four weeks apart (i.e., baseline period), followed by an eight-week intervention period and a post intervention assessment. Subsequently, after 4 weeks a follow-up assessment will be conducted. This will allow the evaluation of baseline stability, the evaluation of the short-term durability of treatment effects, and enhanced statistical power by enabling within-subject modeling.

Eligibility criteria will be assessed during intake assessment prior to enrollment. The participants will be randomly allocated to one of the three intervention arms: (1). HIIT; (2). CAT; (3). MA. Stratified block randomization via CASTOR EDC will be used to minimize selection bias. Randomization will be stratified by disease diagnosis (PD or MS), with six blocks of four participants per diagnosis group allocated sequentially over the course of this study.

This study is approved by the medical ethical review board of the Amsterdam UMC (2021.0476). The current study status: enrollment and data collection. Additionally, blood samples will be collected and stored in the HersenFIT study biobank for future biomarker analyses, as approved by the institutional biobank review committee.

This study was prospectively registered at www.ClinicalTrials.gov (ID: NCT05357638).

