#### 2.2.2. Sample Size

The sample size was calculated based on the primary outcome (HADS total score). Anticipated improvements were 6 points in the HIIT group and 3 points in the CAT group, with an standard deviation (SD) of 6 [64]. Using G*Power (version 3.1) for repeated measures analysis of variance with an alpha of 0.05 and 80% power, a total of 42 participants is required. Accounting for an expected 15% dropout rate, 48 participants will be recruited.

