The outcomes of this study could inform the development of tailored exercise-based interventions in clinical practice. Should HIIT prove superior, it may become a preferred modality in future rehabilitation protocols—though further validation in larger cohorts and across diverse patient subgroups would be needed. Future studies should explore for whom, under what conditions, and for how long HIIT remains effective. A long-term follow-up assessment could provide essential data on the sustainability of intervention effects and the practical challenges of maintaining high-intensity exercise. Furthermore, the inclusion of home-based MA acknowledges real-world barriers to structure exercise, offering a flexible and accessible alternative that could enhance adherence and long-term outcomes.

In conclusion, we present the protocol of a transdiagnostic single-blind randomized controlled trail investigating the effects of HIIT on non-motor symptoms, particularly anxiety and depression, compared with CAT and MA in individuals with PD and MS. The secondary objectives include evaluating the impact of exercise on blood and MRI measures of neuroplasticity, neurodegeneration, and overall quality of life. Ultimately, this study addresses a critical gap in the rehabilitation of people with PD or MS by focusing on non-motor symptoms, which have a profound impact on quality of life but are often overshadowed by motor impairments. By adopting a transdiagnostic approach, the findings could inform the development of generalizable, mechanism-driven interventions that transcend disease-specific boundaries.

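### PD and MS arm effects should be reported with confidence intervals whatever the disease interaction's p-value, because the test that gates them has low power

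*Protocol article*

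**What the plan says.** Section 2.5 (Statistical Analysis) fits linear mixed models with time and arm as fixed factors and states that "interaction effects for disease will be investigated". It does not name the interaction term. It then sets the rule: "Exploratory subgroup analyses will be conducted if the interaction term is significant". The level for all tests is "significance set at *p* < 0.05 (two-tailed)".

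The same section promises model estimates with 95% confidence intervals for all primary and secondary outcomes, but does not say that they will be given by disease. Presentation by disease is promised unconditionally only for baseline characteristics.

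Section 2.1 makes diagnosis the stratification factor: "Randomization will be stratified by disease diagnosis (PD or MS)". Section 2.2 sets 24 participants per disease. Section 3 closes with the hope that "the findings could inform the development of generalizable, mechanism-driven interventions that transcend disease-specific boundaries".

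The sample size in section 2.2.2 is built on the pooled comparison. No power is given for the disease interaction.

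**The concern.** Diagnosis is built into the design, and applicability across the two diseases is the trial's stated ambition. To judge that, a reader needs the arm effects in PD and in MS and a measure of how far they differ. The rule in section 2.5 releases the disease-specific analyses only after a significant test, in a trial with about eight people per arm and disease.

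Two consequences follow if the power is low. In most runs of such a trial the disease-specific effects would not be shown, even if they truly differed by an amount that matters. And in the runs where the gate opens, the difference shown must already be large, so it tends to overstate the truth.

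The article itself gives reason to expect some difference. Section 3 cites pooled depression effects of about 0.71 SD in PD and 0.37 SD in MS, and warns that disease-specific features may be oversimplified.

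**Working it through.** **Inputs from the documents.** Section 2.2.2: "Anticipated improvements were 6 points in the HIIT group and 3 points in the CAT group, with an standard deviation (SD) of 6", so the planned HIIT-CAT difference is 6 - 3 = 3 points on the HADS total. Section 2.5: two-sided 5% level. Sections 2.1 and 2.2: three arms, 24 per disease.

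**Assumptions.** Equal allocation gives 24/3 = 8 per arm and disease, or 42/6 = 7 at the 42 participants the calculation requires. The article does not say whether its SD of 6 refers to scores or to change, so I take 6 as the base case for change and show a range.

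**The plan's own figure.** The statement "with an alpha of 0.05 and 80% power, a total of 42 participants is required" reproduces as a repeated-measures ANOVA, within-between interaction, with d = 3/6 = 0.5, f = d/2 = 0.25, 3 groups, 2 measurements and correlation 0.5 (software default, assumed). The noncentrality is N·m·f²/(1 - ρ) = 42 × 2 × 0.0625/0.5 = 10.5, and power is 0.803. N = 39 gives 0.769. This supports the pooled arm comparison and says nothing about the disease interaction.

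**The gate.** The contrast is (HIIT - CAT in PD) - (HIIT - CAT in MS).

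- Standard error = SD × √(4/n). At SD 6 and n = 8: 6 × √0.5 = 4.24.
- Degrees of freedom = 6(n - 1) = 42; critical t = 2.018.
- Smallest significant observed difference = 2.018 × 4.24 = 8.56 points, almost three times the planned arm difference.

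Power by noncentral t, two-sided 5%:

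| SD of change | How it could arise from a score SD of 6 | 3 points, n = 7 / 8 | 6 points, n = 7 / 8 |
|---|---|---|---|
| 3.8 | one pre, one post, ρ = 0.8: 6√0.4 | 17.5% / 19.4% | 53% / 59% |
| 4.24 | two pre, two post averaged, ρ = 0.5: 6√0.5 | 14.9% / 16.5% | 45% / 50% |
| 6 | one pre, one post, ρ = 0.5 | 9.9% / 10.6% | 25% / 28% |
| 8.5 | one pre, one post, ρ = 0: 6√2 | 7.4% / 7.8% | 15% / 16% |

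**Other readings of the test.** A 2-df arm by disease test with one arm differing by 3 points has 10.0% power at n = 8 and 9.3% at n = 7 (SD 6). As an illustration only, the cited PD-MS gap for depression, 0.71 - 0.37 = 0.34 SD or about 2 points, would be detected with 7.6% power at SD 6 and n = 8 (6-12% over the range).

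**Exaggeration.** If the true difference is 3 points, SD is 6 and n = 8, simulation gives significant estimates that average about 3.4 times the truth in absolute size.

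**What unconditional reporting would show.** Within one disease the HIIT-CAT standard error is 6 × √(2/8) = 3.0, so the 95% half-width is about 6 points. For the interaction it is about 8.6 points.

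**The case against.** The strongest reply is that gating is a recognised guard against over-reading small subgroups, that section 2.5 already labels these analyses exploratory, and that comparisons of 8 with 8 with intervals of about ±6 points cannot establish or refute a common effect. This is fair, but the exploratory label gives the same protection without withholding the estimates, and the width of the intervals is itself what a reader needs to see before accepting a cross-disease claim.

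Second, the rule governs subgroup analyses, not the interaction estimate. The general promise of model estimates with 95% CIs may well cover the latter. That stands, though it does not reach the PD and MS arm effects.

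Third, a reader might infer that the transdiagnostic conclusion will rest on a non-significant interaction. The article does not say so. Its closing claim is conditional, section 3 acknowledges that heterogeneity complicates interpretation, and it asks for validation in larger cohorts and diverse subgroups before HIIT is preferred.

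Fourth, a reader might infer that the test could hardly ever be significant. That goes too far. If HIIT beat CAT in one disease only and the pooled effect were the planned 3 points, the diseases would differ by 6 points (6 against 0), and power would be 28% at SD 6 and up to 59% at the most favourable SD. A difference of 12 points would be detected with 79% power at SD 6.

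Finally, the interaction term is unnamed. A disease by time term over all arms (24 against 24) would have about 40% power for 3 points, but it does not test whether the treatment effect differs by disease.

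**Conclusion.** The point holds as a low-cost improvement to the reporting of exploratory results. The rule in section 2.5 is a weak gate: 11% power for a between-disease difference as large as the whole planned HIIT-CAT effect and 28% for twice that, at SD 6 with 8 per cell. With 7 or 8 per cell and change SDs from about 3.8 to 8.5, the ranges are 7-19% and 15-59%. Only the largest of these differences combined with the smallest SDs brings the chance of opening the gate to about one half or more.

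These figures rest on equal allocation, on HIIT against CAT as the contrast (no effect is given for MA), and on the assumed change SDs. The primary pooled comparison is not affected. The plan does not announce that non-significance will be read as similarity; the weakness is that it commits to no other look at whether PD and MS agree.

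**What to change.** Replace the gating sentence in section 2.5 with:

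*Arm effects on change in HADS will be estimated for PD and MS from the mixed model with arm, time and diagnosis interactions and reported with 95% CIs, together with the interaction estimate and its CI, regardless of the p-value; these are exploratory, and a non-significant interaction will not be taken as evidence of similar effects.*

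This also settles which interaction is meant. The cost is one sentence and one extra table of wide, exploratory intervals. No additional participants or data are needed. Section 2.1 gives the study status as enrollment and data collection, so the change can still be specified before results are known.
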